**Methods:**

• Metabolic profile, hyperinsulineamic eugluceamic clamp, muscle and fat biopsies, blood tests, maximum oxygen uptake, DEXA scan

**Primary end-points:** Proteomics analysis of serum

**Secondary end-points:** Substrate metabolism, fiber typing, and activation of satellite cells

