2003). In addition, gene doping is also a future drug strategy one will have to deal with. Stable transfection of the Epo gene in tissue has already been shown in animal models (Hojman et al., 2007). Gene doping was therefore in 2003 added to WADA and the IOC's list of "Prohibited Substances and Methods in Sport"(Pascual et al., 2004). This stresses the importance of developing new and more sensitive Epo analysis. Thus, future anti-doping tests should not only focus on detecting rHuEpo and its derivatives, but also on biological markers that change by Epo exposure. Such markers have been studied. Total hemoglobin mass and reticulocyte percentage (_OFFhr-score_) and the so-called blood-passport (Gore et al., 2003) have been suggested as markers for Epo abuse. The problem with the OFF_hr-score_ is that the cut-off values are based on the average population level, and because of large inter-individual differences the cut-off values (upper and lower limit) are very broad, in order to avoid false-positive results. This ultimately leads to a low detection level (Lundby & Robach, 2009; Borno et al., 2010). Also the blood pass, where one follows the athletes’ blood values over time, proved not to guarantee a drug free sport (Borno et al., 2010).

Proteomics has proven to be a good way to characterize all proteins expressed in a biological system, such as blood. We have already in a previous study showed that 16 days of treatment with rHuEpo resulted in significant changes in several serum proteins (Christensen et al.

2010). The main objective of this project is to investigate the effect of prolonged rHuEpo treatment on changes in the serum proteome of healthy young men. Furthermore, we want to investigate the effect of rHuEpo and physical activity on these markers, as it is important to elucidate the effect of physical activity, if these markers should be used as anti-doping markers in the future.

Epo receptors are found in a variety of different types of tissues other than the bone marrow, including neurons, astrocytes, microglia, cancer cells, gastric mucosal cells and especially muscle tissue. The effect of Epo in these tissues still needs to be fully elucidated.

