**PURPOSE**

To identify new serum biomarkers to detect abuse of rHuEpo. Secondarily, we want to examine the effects of 10 weeks of rHuEpo treatment and training on a wide range of other parameters e.g. turnover of fat, carbohydrate, and protein, muscle type changes, and activation of satellite cells in skeletal muscle.

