**DESIGN**

• The experiment is a single-blind, randomized study.

• 40 subjects in total will be included and randomly assigned to one of the following groups (n = 10);

o Placebo treatment

o Placebo treatment + endurance training

o rHuEpo treatment

o rHuEpo treatment + endurance training

• Subjects are examined before and after 10 weeks of rHuEpo/placebo treatment, and after a 3 weeks washout period.

• EPO (Darbepoietin alpha) (~50IU/kg)/placebo (saline) is administered s.c. twice a week for the first 3 weeks at a dosage of 2x40 μg, and once a week from week 4-10 at a dosage of 20 μg.

• The endurance training will consist of 1 to 1.5 hours of cycling at 65-80% of VO_2_max, 3 times weekly. This was previously shown to cause an increase in maximum oxygen uptake (Midgley et al., 2006).

[figure not shown]

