**BACKGROUND**

Erythropoietin (Epo) is produced in the kidneys when the oxygen levels in the blood become too low. Epo stimulates the formation of new red blood cells in the bone marrow. Epo is used as a medicine for kidney and cancer diseases, leading to a lack of red blood cells.

Epo increases red blood cell production and hence the amount of oxygen that can be transported around the body. It is shown that prolonged use of synthetic Epo (rHuEpo) leads to an increase in the period of time a given physical work can be performed, therefore it will continue to be abused by athletes, especially in endurance sports. This happens despite the fact that rHuEpo was added to the anti-doping list already in 1990. It is therefore important to find a robust method to detect this abuse. Not only to ensure fair competition but also to reduce the abuse and the side effects that follow, e.g increased risk of blood clots.

The existing method for measuring the abuse of rHuEpo approved by the World Anti-Doping Agency (WADA) is based on differences in the sugar groups bound to rHuEpo and Epo produced in the body, respectively. Whether this approach will be effective against new synthetic Epo products are still unknown. Future Epo tests should therefore be based on biological markers, that changes when Epo levels rise. Various blood markers related to the amount of red blood cells have already been investigated, but these methods have proven to be very conservative, since the boundaries of the normal range is very wide in order to avoid false-positive results.

Proteomics is a method by which you can look at all the proteins in blood at the same time. Even proteins that have changed very little can be distinguished. The main objective of this project is to investigate the effect of prolonged treatment with rHuEpo on changes in blood proteins in healthy young men. We have in a previous study with 16 days of treatment with rHuEpo shown changes in blood proteins. It is hoped that some of these proteins can be used as marker for Epo abuse in the future. We furthermore want to explore the effect of physical activity on these proteins, since athletes will always be physically active. The effect of physical activity itself is therefore important to elucidate, if these proteins should be used in a future anti-doping test.

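### The sponsor already has candidate serum proteins, but the plan judges them by the same unadjusted p<0.05 rule as every other protein

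*Protocol*

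**What the plan says.** The Background of the protocol states that "16 days of treatment with rHuEpo resulted in significant changes in several serum proteins". It then gives the main objective, to "investigate the effect of prolonged rHuEpo treatment on changes in the serum proteome of healthy young men", and adds: "Furthermore, we want to investigate the effect of rHuEpo and physical activity on these markers".

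The Background of the layman description is more direct. Straight after mentioning the earlier 16-day study it says "It is hoped that some of these proteins can be used as marker for Epo abuse in the future", and then "We furthermore want to explore the effect of physical activity on these proteins".

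The Purpose section begins "To identify new serum biomarkers to detect abuse of rHuEpo". The primary end-point, listed under Methods in the Design section, is "Proteomics analysis of serum". It names no protein, contrast or time point.

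The Serum paragraph schedules proteomics at baseline and on days 21, 71 and 92. The Statistics section offers t-tests, ANOVA or non-parametric equivalents, and paired tests within groups, with a single threshold of 0.05 for significance. No adjustment for multiple testing is mentioned, and the earlier proteins are neither named nor counted.

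On size, the Design section says "40 subjects in total will be included and randomly assigned to one of the following groups (n = 10" per group. There are four groups: placebo or rHuEpo, each with or without training.

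**The concern.** Proteins that already moved under rHuEpo have a prior hypothesis; the rest of the proteome does not. A protein first seen in a group of 8 subjects that changes again in a randomised, placebo-controlled comparison is much stronger evidence than a fresh hit from a screen, provided its test was fixed in advance and its error rate controlled.

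The plan draws no such distinction. One unadjusted rule covers a handful of prior candidates and an unspecified number of untargeted proteins, at three post-baseline days. A renewed change in a known candidate then carries no stated error rate, and the list of new hits will mix real changes with chance ones. The trial could report on the candidates under proper error control at almost no cost, and that option is lost once the results have been seen.

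**Working it through.** **What can be reproduced.** The protocol gives no effect size, SD, power, number of earlier proteins or number of proteins to be measured, and says that no power calculation was possible. There is no stated figure to reproduce. The calculations below illustrate the consequence of the text.

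**Inputs from the protocol.** Four groups of 10, so pooling over training gives 10 + 10 = 20 rHuEpo against 20 placebo. Significance level 0.05 per test.

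**Assumed inputs.** Two-sided tests; independent proteins; 5 to 10 earlier candidates (the protocol says only that there were several); 100 to 1000 measured proteins; a true effect of 1 SD; 10 truly changed proteins in the screen.

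**Step 1: the rule as written.** Expected false positives among m unchanged proteins, per contrast = 0.05 × m.
- m = 100: 0.05 × 100 = 5
- m = 500: 0.05 × 500 = 25

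Chance of at least one false positive among m independent unchanged proteins = 1 − 0.95^m.
- m = 5: 1 − 0.95^5 = 0.226
- m = 10: 1 − 0.95^10 = 0.401
- m = 100: 1 − 0.95^100 = 0.994

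So even the short candidate list, tested alone, would carry a family-wise error of about 23 to 40%.

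**Step 2: power under the rule as written.** For a 20 v 20 t-test the noncentrality is d × √(20 × 20 / 40) = d × √10, with 38 degrees of freedom. At d = 1 and two-sided 0.05, power is 0.87. The plan as written therefore does not lack power for a candidate with that effect; it lacks error control.

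**Step 3: two ways to add error control (simulated, 20 v 20, 1 SD).**

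| Procedure | Setting | Average power per truly changed protein |
|---|---|---|
| Holm 5%, candidates only | 5 candidates, all changed | 0.80 |
| Holm 5%, candidates only | 5 candidates, 2 changed | 0.69 |
| Holm 5%, candidates only | 10 candidates, all changed | 0.73 |
| Holm 5%, candidates only | 10 candidates, 5 changed | 0.62 |
| Benjamini-Hochberg 5%, whole screen | 100 proteins, 10 changed | 0.50 |
| Benjamini-Hochberg 5%, whole screen | 300 proteins, 10 changed | 0.31 |
| Benjamini-Hochberg 5%, whole screen | 1000 proteins, 10 changed | 0.17 |

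As a check on the Holm range, the noncentral t gives power 0.673 at 0.05/5 = 0.01 and 0.576 at 0.05/10 = 0.005. These are the Bonferroni values, and Holm must do at least as well.

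**Step 4: sensitivity.** The gap depends on the assumptions. With 30 truly changed among 100 proteins, Benjamini-Hochberg power is about 68%, inside the Holm range. With 10 changed among 50 it is about 62%, the lower end of that range. At an effect of 1.5 SD it rises to about 95%, 91% and 80% for 100, 300 and 1000 proteins.

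**The case against.** The strongest case against runs as follows.

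- **Discovery is the declared aim.** The Purpose speaks of new biomarkers and the main objective is the whole serum proteome. The phrase about markers in the Background follows that objective and may mean whatever this trial finds. The clearer wording is in the layman description and concerns exploring the effect of exercise. A reader might infer that the protocol promises to follow up the earlier proteins; the text does not go that far. This stands, and it is why the fix leaves the discovery purpose in place.
- **The trial is not bare repetition.** A reader might also infer that it merely repeats discovery and can confirm nothing. The documents do not support that. The design adds randomisation against placebo, training arms, 10 weeks of treatment and a washout sample. The generic group comparisons can be applied to the earlier proteins, and these can be looked up in the publication that the protocol cites. This stands too.
- **The power contrast is not the protocol's own.** The protocol states no false-discovery procedure, so as written the candidates do not compete with the proteome for power; the unadjusted test has the higher power (0.87). This stands. The lower figures show only what happens if error control is later imposed on all proteins together.
- **Test detail may sit in an analysis plan.** True of the Holm step and the choice of day. But the protocol itself fixes an assay as primary end-point and a flat 0.05 rule for significance, and those are what need changing.
- **The candidates arose after 16 days, not 10 weeks.** This is a reason to choose the deciding day with care, not to leave the candidates without a test.

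**Conclusion.** The point holds in a limited form. The sponsor has candidate proteins and signals interest in them, yet neither the primary end-point nor the Statistics section gives them an error-controlled test.

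The part that rests on the protocol's own 0.05 threshold is firm: about 5 false positives per 100 unchanged proteins per contrast. The 23 to 40% family-wise error within the candidates depends on assuming 5 to 10 of them, independent, none truly changed. The power comparison, about 62 to 80% for a Holm-adjusted candidate family against about 17 to 50% across 1000 down to 100 proteins, is illustrative. It assumes a 1 SD effect and 10 truly changed proteins in the screen, and it narrows with larger effects or more changed proteins.

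This should be changed, but it does not make the design unsound.

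**What to change.** Before any sample is analysed:

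1. Keep the discovery of new markers as a purpose.
2. In the primary end-point, or in the analysis plan, list by name the serum proteins reported as changed in the earlier study and declare them the pre-specified candidate family.
3. Test them on the randomised rHuEpo-versus-placebo comparison (20 v 20) at one proteomics day chosen in advance from days 21, 71 and 92, Holm-adjusted at 5%.
4. Report the effect of training on each candidate as an estimate with a confidence interval.
5. In the Statistics section, replace the unadjusted 0.05 rule for all other proteins with a stated false-discovery-rate control, and label those results discovery.

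The cost is about a paragraph of wording, with no extra subject, sample or assay. There are two downsides. Hits outside the list carry the weaker label of discovery. Candidates also give up some power compared with an unadjusted test: from about 0.87 to about 0.62 to 0.80 in the illustration.

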**SUBJECTS**

A total of 40 healthy young men will be included in the present study. These will be recruited through the web page www.forsøgsperson.dk and various notices on educational institutions in Aarhus (see attached notice).

Because the effect of rHuEpo on some of the required parameters have not previously been elucidated, it has not been possible to make a power calculation. However, from similar studies in our laboratory, it is estimated that approximately 10 subjects in each group is enough to reach statistical power. Furthermore, in a previous study on a group of 8 subjects it was possible to detect significant changes in the proteome 16 days after treatment with rHuEpo (Christensen et al., 2010).

**Inclusion Criteria:**

• Written consent before study start

• Adult, healthy men

• Age >18 years and <35 years

• Normal weight (BMI: 18-27)

• Untrained (<2 hours of physical activity per week)

• Non smoking

**Exclusion Criteria:**

• Chronic disease

• Blood pressure above 135/85

• Hematocrit above 45%

**Participants will be excluded from the study if:**

• They want to end their participation.

• The investigator finds that the participant fails to conduct the experimental procedures or because of security reasons.

• Participants develop severe or intolerable side effects. If so, the experiment for each participant will be stopped and the investigator will refer to appropriate treatment. Hereafter, it is considered whether the trial must be terminated.

The participant may withdraw from the trial at any time. Data obtained from discontinued subjects will be used, if possible - it will depend on the duration until termination of participation. The data it is possible to analyze will be used.

**METHODS**

**Medical examination:** Thorough objective medical examination involving anamneses, measurement of blood pressure, waist circumference, weight, height, ECG, and routine blood tests. Routine blood tests will be obtained before starting the experiment, in order to ensure that the participants are healthy. The following will be measured; Hemoglobin, erythrocytes, iron, transferrin, ferritin, reticulocytes, haptoglobin, albumin, alkaline phosphatase bilirubin, LDH, plasma hemoglobin, ALT, potassium, sodium, creatininium, leukocytes, platelets, CRP, HbA1c, cholesterol, TSH, GFR.

**Maximal oxygen uptake:** Maximal oxygen uptake will be measured at least one week before the first metabolic day, on the same day as the screening blood tests are collected and the medical examination are carried out. The subjects will be re-tested again halfway through the training period and at the end of the study, the day after the final metabolic day. The subjects will be tested on an ergometer bicycle by indirect calorimetric. The aim is to achieve maximal oxygen uptake after approx. 5-7 min.

**DEXA scan:** Body composition will be measured by dual-energy X-ray absorptiometry (DEXA) on a Hologic Discovery prior to treatment and at the end of the treatment period.

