• **Biopsies:** Biopsies are taken one hour after the start of the metabolic profile and 30 minutes into the hyperinsulineamic clamp. *Fat Biopsies:* Subcutaneous fat is aspirated from the abdomen with a liposuction needle under local anesthesia and some of it is immediately frozen in liquid nitrogen. The remaining fat cells are purified by collagenase and stained with methylene blue for visualization of nukleii and cell membrane. Fat cell size is determined with a microscope and a camera is used to take pictures. *Muscle Biopsies:* A muscle biopsy is taken from the vastus lateralis with a Bergström needle. After 10-15 min. of local anesthesia (1% lidocaine), incision is made through skin and muscle fascia app. 15-20 cm above the knee. Muscle tissue is obtained and immediately frozen in liquid nitrogen or embedded in Tissue Tek and frozen. *Analyses:* Western Blot, PCR, immunohistochemical analysis, and intramuscular TG and glycogen.

• **Blood tests:** Blood samples are obtained every 20 minutes during the metabolic day. Total blood loss is around 320 ml. *Analysis:* Epo, total, free and bioactive IGF-I, IGFBP-1, glucose, insulin, C-peptide, free fatty acids, adiponectin, VLDL-TG, metabolites, glucagon, cortisol, catecholamines, albumin, phenylalanine enrichment, glucose specific activity, glycerol, lactate, ALT, alkaline phosphatase, bilirubin, pro-thrombin index, carbamid, ghrelin, and proteomics

• **VLDL studies:** These studies will be conducted before and after the 10 weeks intervention. 1 week in advance 60 ml of venous blood is sampled under sterile conditions. VLDL-TG will be insulated by ultracentrifugation (40000 g for 18 hours at 10 °C) and subsequent labeled with 20 μCi [1-^14^C] triolein. Sterility will be secured with cultivation before the sample is used for reinfusion. On the study day, the patient's own ex-vivo labeled VLDL-TG will be infused (autologous infusion) until steady state (4 hours). Blood samples will be obtained every 10 min over the last 30 min for determination of VLDL-TG SA and concentration.

• **VLDL-TG oxidation:** These studies will be performed before and after the 10 weeks intervention. VLDL-TG oxidation is measured by collecting expired air with hyamin-trapping for analysis of ^14^CO_2_, this is measured before the start of the metabolic day and 3 times during the last half an hour of the basal period.

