When placing the intravenous catheters for blood collection and infusion there is a very small risk of infection and subjects are instructed to contact the investigator by redness and soreness corresponding to the injection sites. There is a small risk of hypoglycemia during and after the hyperinsuliniemic euglyceamic clamp. The risk is minimized by insuring a stable blood glucose level before the subject leaves the research laboratory. In addition, subjects are informed about symptoms of hypoglycemia and the subjects are given tablets with grape sugar for intake in the case of hypoglycemia.

Serious event or serious adverse event: an event that at any dose results in death, is life threatening, requires hospitalization, or prolongation of existing hospitalization, results in persistent or significant disability. If a serious event/adverse event appears this is reported to the Medicines Agency and the Ethics Committee. In case of a severe event the trail is immediately stopped and treatment commenced. The subject is followed until symptom free and/or the condition is stable. All adverse reactions/incidents will also be indicated in the final report. Complications will be recorded in connection with aforementioned medical examination and the subject will be treated at the research laboratory, since the trial is conducted in a highly specialized hospital.

The total blood loss at each experimental day is about 320 ml. There is 10 weeks between each experimental day, thus, this blood loss is not expected to induce symptoms. For comparison, an ordinary blood donation is approx. 500 ml. In addition, around 5 ml of blood will be collected on days 8, 15, 21, 36, 50, 64, 71 during the treatment period and at days 78 and 92 during the washout period, in order to monitor the hematological values. In addition, the participants will give 60 ml of blood for labeling of VLDL 1 week before the last experimental day. Blood loss in total throughout the study will be approximately 850 ml during a 4 months period.

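### Final VO2max is tested the day after blood loss and thigh biopsies, while the baseline and halfway tests are not, so within-arm changes to the final test are biased downward

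*Protocol*

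**What the plan says.** Protocol, METHODS, Maximal oxygen uptake, sets three tests on an ergometer bicycle. For the first: "Maximal oxygen uptake will be measured at least one week before the first metabolic day", on the screening day. Subjects are then tested again midway through training and "at the end of the study, the day after the final metabolic day".

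The Metabolic profile part of METHODS describes what a metabolic day involves. On blood: "Total blood loss is around 320 ml". On tissue: "Biopsies are taken one hour after the start of the metabolic profile and 30 minutes into the hyperinsulineamic clamp", and "A muscle biopsy is taken from the vastus lateralis with a Bergström needle". SAFETY adds "60 ml of blood for labeling of VLDL 1 week before the last experimental day". It also warns of mild pain at the biopsy site over the first few days. It says the blood loss should cause no symptoms, but does not consider its effect on a maximal exercise test.

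The METHODS part of the layman description places metabolic days only before treatment and after 10 weeks, so none comes shortly before the halfway test. STATISTICS plans paired tests within groups, and t-tests, ANOVA or non-parametric equivalents between groups, at the 0.05 level. The end-points listed under DESIGN are serum proteomics (primary) and substrate metabolism, fibre typing and satellite-cell activation (secondary). VO2max appears there only among the methods.

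**The concern.** A pre-post comparison needs both measurements taken under the same conditions. Here the baseline test comes before every invasive procedure, and the halfway test is well clear of them. The final test follows within a day of a sizeable blood draw and biopsies of a working muscle. Less blood and a sore thigh would each be expected to lower a maximal cycling result, and nothing in the schedule pushes the other way.

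The DESIGN section justifies the training regimen by its known effect on maximal oxygen uptake, so VO2max is the natural check that training worked. A real gain in an arm could be understated. An arm with no true change could appear to decline. A fall from halfway to final could be read as loss of effect when it comes from the procedures. The disturbance is built into the measurement, so no later analysis of a single arm can separate it from a true change.

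**Working it through.** The protocol gives no effect size, standard deviation or power for VO2max, so there is no planned figure to reproduce. The check has four steps.

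**1. Conditions at each test (from METHODS, SAFETY and the layman description)**
- Baseline: a week or more before the first metabolic day.
- Halfway: no metabolic day shortly before it.
- Final: one day after about 320 ml of blood loss and vastus lateralis biopsies, within the period in which the protocol itself expects soreness.

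**2. Share of blood removed**

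Share = loss / blood volume. The loss of 320 ml is from the protocol. The blood volume is assumed.
- At 6 litres: 320/6000 = 5.3%. At 5 litres: 320/5000 = 6.4%.
- Over a wider assumed range of 6.5 to 4.5 litres: 320/6500 = 4.9% to 320/4500 = 7.1%.
- Adding the 60 ml drawn a week earlier, as if none had been replaced: 380/6000 = 6.3% to 380/5000 = 7.6%.

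If plasma volume is fully restored by the next day, haematocrit falls by the same proportion. Full refill is an upper bound on dilution. With less refill, circulating volume is lower instead, so the expected direction is the same.

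**3. What this does within arms and between arms**

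SAFETY cites a haematocrit rise from 45% to 49% in an earlier study of a similar regimen. Apply the same dilution to both values:
- Loss of 5.3%: 49 × (1 − 0.0533) = 46.4 and 45 × (1 − 0.0533) = 42.6. The gap is 3.79 of 4 points.
- Loss of 6.4%: 49 × (1 − 0.064) = 45.9 and 45 × (1 − 0.064) = 42.1. The gap is 3.74 of 4 points.

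About 94% to 95% of the gap between a treated and an untreated subject is kept.

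The same holds for VO2max change. A common additive bias c cancels: (Δ₁ − c) − (Δ₂ − c) = Δ₁ − Δ₂. With a common proportional loss f, a true relative change a is observed as (1 + a)(1 − f) − 1, and the difference between arms becomes (1 − f)(a₁ − a₂). For an illustrative true difference of 10 points, f = 2% leaves 9.8 and f = 7% leaves 9.3. Within an arm the effect is much larger. At f = 5%, a true 10% gain is seen as 1.10 × 0.95 − 1 = 4.5%, and no change is seen as −5%.

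**4. Effect on the paired test**

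Inputs are n = 10 per arm (DESIGN) and α = 0.05 (STATISTICS; two-sided is assumed). The bias b is in standard deviations of the within-subject change, and its values are illustrative. Rejection probabilities come from the non-central t distribution with 9 degrees of freedom and non-centrality (true change − b) × √10.

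| Bias b | No true change: declared significant | True gain of 1 SD: power |
|---|---|---|
| 0 | 5% | 80% |
| 0.25 | 11% | 56% |
| 0.5 | 29% | 29% |
| 1.0 | 80% | 5% |

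**The case against.** The strongest reply is that little of importance depends on this comparison, and much of it stands.

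- VO2max is not a primary or secondary end-point, so no named result is affected.
- All four arms follow the same schedule, so the randomised comparison of change is largely protected. An apparent decline under placebo is exactly what the placebo arms are there to reveal. Soreness that varies between subjects could still add noise.
- Baseline to halfway is free of the problem and gives a largely clean within-arm check.
- The protocol calls the biopsy pain mild and expects no symptoms from the blood loss. That speaks to tolerability, however, and does not make the tests comparable.

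Three stronger readings are tempting, but the documents do not support them.

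- A reader might infer that VO2max is the only physiological check on the interventions. The Serum paragraph of METHODS schedules haemoglobin, erythrocytes and reticulocytes from baseline to day 92, which checks the Epo effect directly.
- A reader might infer that the blood loss erases most of the Epo effect, since 49% would fall to about 46% (a loss of 2.6 to 3.1 of the 4 points). That compares a bled final value with an unbled baseline, assumes full plasma refill, and borrows the rise from another study. Between arms, nearly all of the gap remains.
- A reader might convert the blood loss into a percentage fall in VO2max. That needs an assumed relation between red-cell mass and VO2max, which the documents do not give.

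**Conclusion.** The point holds as a scheduling flaw of limited reach. Within-arm VO2max changes from baseline to final and from halfway to final are biased downward, because only the final test follows a metabolic day.

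The direction follows from the protocol's own schedule together with the ordinary expectation that recent blood loss and a sore thigh lower a maximal cycling test. The size cannot be derived from the documents. The figure of 5.3% to 6.4% of red-cell mass rests on an assumed blood volume of 5 to 6 litres, and the dilution figures are upper bounds. The error rates for the paired test show what a given bias would do; they do not estimate the bias.

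The primary proteomics result, the named secondary end-points and the baseline-to-halfway VO2max change are not affected. Between-arm differences in change are only slightly affected. This is a cheap improvement to the plan and does not threaten the trial's main conclusions.

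**What to change.** Hold the final VO2max test before the final metabolic day, at the interval used at baseline (one week or more), and state that it comes before the 60 ml blood draw for VLDL labelling. That draw falls one week before the last experimental day, so the interval alone does not settle the order. The VLDL paragraph in METHODS can be read as placing such a draw ahead of the first metabolic day as well, so fix the same order at both ends.

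No test is added and only the visit schedule changes. The small downside is that the final value is taken about one week before treatment ends.

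If the timing cannot be changed, state in the plan that conclusions involving the final VO2max test rest only on between-group differences in change, and that within-group change is assessed from baseline to halfway.
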